#### **4.3.7 What is the planned recruitment rate?**

Each RHC has at least 100 registered patients with hypertension/ diabetes. We anticipate recruiting 50% of them, to generate 50 participants. The recruiting process will take less than two weeks as all are existing patients registered in RHCs.

#### **4.3.8 How will source of bias and risks be taken account of?**

Potential sources of bias include 1) that this is an open label trial; and 2) non-compliance of health providers and patients. We have described measures to mitigate the risk of an open label trial in 4.2. We will provide ECHO-based remote training and supervision with health providers to identify non-compliance and provide timely feedback. Patient champions will connect patients or their relatives who have low literacy in smart phones or do not attend virtual consultations. In addition, we will provide gender sensitive support. The key risk is change in provincial level commitment of the NCD Prevention and Control Program due to staff turnover or other events. The mitigation strategy includes to: 1) document the relationship; 2) keep the NCD Program continuously engaged; and 3) continue the technical assistance for sustained public funding.

**4.4 Process Evaluation:** We aim to describe health system and service delivery context in which the interventions are implemented, explore delivery and dose of intervention components received, and understand mechanisms of impact and unanticipated consequences on health providers and parents. This

fits into the qualitative indicators set up in the RE-AIM dimensions. Methods will include document review (e.g., meeting minutes), observations of training sessions, and qualitative interviews with stakeholders. Specifically, we aim to understand: 1) *Reach*: the recruitment process and the program inclusion; 2) *Effectiveness (feasibility and acceptability)*: to what extent our measures are understood and accepted by patients; 3) *Adoption*: changes of interventions made at the facility level; how the NCD-COVID care connects with other programs such as tuberculosis and immunization; and any resistance from structural, professional or personal factors in adopting the change; 4) *Implementation*: issues related to fidelity/quality of implementing the NCD-COVID program, and any unanticipated consequences; 5) *Maintenance*: to what extent the NCD-COVID program is institutionalized in different RHCs. We will also conduct spatial analysis to understand how patients travel time to RHCs may affect their care utilization and BP control levels. We will conduct a mixed methods process evaluation using program record review, interviews, and observations, with a broad section of patients, family members, peers, health providers and health policymakers. Previous similar work by [name] in China, and [name] in the Philippines, will inform this evaluation. The data will be analyzed using a thematic approach, reported based on Consolidated Criteria for Reporting Qualitative Studies (COREQ).

**4.5 Cost-effective analysis:** An incremental cost effectiveness analysis will be conducted to estimate the added benefits of the intervention regarding extra 1% of patients with blood pressure under control versus usual care from a societal perspective, which entails an assessment of all resource costs irrespective of payer. Costs associated with intervention over and above usual care (excluding research costs) will be collected and used together with the above effectiveness/outcome measures to calculate the incremental cost-effectiveness ratio. Costs will include capital costs such as training, other costs to strengthen the capacity of providers to deliver enhanced services, and recurrent costs such as drugs and laboratory tests. Salaries of staff in RHCs will be included in case of extra working time is sought in some clusters during the intervention. Project record review and interviews with managers will be conducted to obtain cost data. Hospitalization and any loss of workdays due to hypertension, diabetes or COVID related illness, as well as time costs associated with participants' travel and waiting time will be recorded and converted into monetary forms using conventional age-sex adjusted market wages. We will use net benefit regression framework which will allow us to adjust for potential confounders and to calculate the clustered standard errors using the sandwich variance estimators to account for a clustered randomized design. Markov models will be used to simulate possible future states of the intervention, and to capture possible longer-term health outcomes (e.g. additional years of life) and associated costs of care.

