#### **4.3.4 The intervention package of care contains:**

- **Integrated NCD-COVID guidelines** to support RHC staff to deliver COVID care by triaging symptomatic patients; promoting rational use of personal protection equipment (PPE); promoting COVID vaccination; replacing face-to-face follow-ups by virtual consultation; and providing case management, health education, and home quarantine support. We will adapt our LMICs COVID-19 guideline into Pakistan to be embedded in the NCD (diabetes/ hypertension) care in the WDF project.
- **A telemedicine platform** containing a smart phone app component, to link patients with facility staff and community peers (champions). The technology will offer patients: a) access to knowledge on NCD and COVID care, including healthy lifestyle and behaviours to prevent COVID transmission; b) report care challenges being faced at respective RHCs (or at the referred facility); c) get peer-support (through technology assisted audio tele-conference of patient groups) for practicing recommended behaviours at home/ communities; d) get routine NCD follow-up advice; also seek advice on medical complaint/ condition. We will also explore the feasibility of using auto-generated messages through the digital application.
- **An ECHO based online platform** for staff training, mentoring and performance monitoring will be employed for case-based learning using best practice and data. RHC staff will be trained in screening, prevention and integrated management of Covid-19 and NCD, as well as how to use the mobile app and send health promotional SMS messages. Based on our experience in the Philippines and Sri Lanka, we will provide training to RHC staff and community health workers regarding how to improve vaccine confidence among high-risk groups for COVID-19, including NCD patients.

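### The costing rule for health-centre salaries (Protocol section 4.5) does not deliver the societal perspective that the same section declares

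*Protocol*

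**What the plan says.** Section 4.5 of the Protocol sets the analysis "from a societal perspective, which entails an assessment of all resource costs irrespective of payer". It limits collection to the increment: "Costs associated with intervention over and above usual care (excluding research costs) will be collected". The provider-side items it names are these: "Costs will include capital costs such as training, other costs to strengthen the capacity of providers to deliver enhanced services", plus recurrent items such as drugs and laboratory tests. Salaries have their own rule: "Salaries of staff in RHCs will be included in case of extra working time is sought in some clusters during the intervention". On the patient side, "time costs associated with participants' travel and waiting time will be recorded and converted into monetary forms". The sources are stated briefly: "Project record review and interviews with managers will be conducted to obtain cost data".

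Section 4.3.4 describes what RHC staff will do in the intervention arm. The guideline component includes triage of symptomatic patients and "replacing face-to-face follow-ups by virtual consultation; and providing case management, health education, and home quarantine support". The ECHO platform, "for staff training, mentoring and performance monitoring will be employed for case-based learning using best practice and data", adds mentoring of staff. Section 4.3.3 says that none of the package's components will run in control facilities.

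**The concern.** The package works largely by changing how RHC staff spend their time. Some tasks are added in one arm only, and some clinic visits are meant to become virtual contacts. A rule that brings salaries in only when extra working time is sought ties the cost to a staffing request rather than to the resources used. Two clusters delivering the same care would carry different staff costs if only one of them sought extra hours.

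The incremental cost is the numerator of the ratio that section 4.5 will report per additional percentage point of patients with controlled blood pressure. Objective 3 is meant to support scale-up, so a reader will take a ratio labelled societal to include the staff time needed to run the service.

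**Working it through.** The Protocol gives no wage, staff-time or cost-effectiveness figure, so there is no stated number to reproduce. The check is first textual and then illustrative.

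**Text, side by side (section 4.5 unless noted)**

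- Declared perspective: all resources, regardless of payer.
- Scope: costs above usual care. Mentoring, virtual care and the added COVID tasks belong to a package withheld from control RHCs (section 4.3.3), so staff time on them falls within this scope.
- Salary rule: included if extra working time is sought. Nothing else in the Protocol values staff time used in normal hours.
- Credit for released time: none stated, although section 4.3.4 intends virtual contacts to replace visits.
- Patient time: valued, although nobody is billed for it. Opportunity cost is thus applied to patients but not to salaried providers.

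Restricting the analysis to increments does not remove the conflict. From a societal perspective, salaried time moved to a task that exists in one arm only has an opportunity cost, with or without extra hours.

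**Illustration of scale**

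Inputs from the Protocol: 15 clusters per arm and 50 recruits per cluster (section 4.3.6), so 15 x 50 = 750 intervention patients; 10 months of follow-up (section 4.3.5); at least 3 doctors and 5 allied workers, so 8 staff per RHC (section 4.3).

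Assumed inputs, not in the Protocol: one virtual contact per patient per month, 10 minutes per virtual contact, 15 minutes per replaced visit, and 1 to 4 hours of in-hours mentoring per staff member per month.

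Consultation hours = patients x months x minutes / 60.

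- Virtual time used: 750 x 10 x 10 / 60 = 1,250 hours.
- Visit time released if every contact replaces a visit: 750 x 10 x 15 / 60 = 1,875 hours.
- Net if all are replaced: 1,250 - 1,875 = -625 hours.
- Range of unvalued consultation time: -625 hours (all replaced) to +1,250 hours (none replaced). Divided by 15, that is about -42 to +83 hours per RHC over 10 months.

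Mentoring hours = RHCs x staff x months x hours per month.

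- Low: 15 x 8 x 10 x 1 = 1,200 hours.
- High: 15 x 8 x 10 x 4 = 4,800 hours.
- If all mentoring is already captured as a training or capacity cost, the unvalued part is 0.

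Taken together, the illustration runs from -625 + 0 = -625 hours to 1,250 + 4,800 = 6,050 hours. Unvalued mentoring and added COVID tasks can only understate the intervention's cost. The consultation part can go either way.

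**The case against.** The strongest reply is that the salary sentence is ambiguous. It follows a sentence about costs above usual care, so extra working time might mean any time beyond usual care, not only hours outside the normal day. The cost lists are also open-ended, and training and capacity costs are counted, which may cover some mentoring. This stands in part: it would be wrong to say that mentoring and virtual care cost nothing in the analysis. But extra time that is sought in some clusters reads most naturally as additional hours requested. Even on the generous reading, released clinic time is not credited and the sentence needs rewording.

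The illustration can be challenged too. Virtual consultation is an option (section 4.3.4), 20% loss is allowed for (section 4.3.6), and the primary outcome needs monthly RHC readings in the last three months (section 4.3.5). If those three contacts are in person, virtual time is 750 x 7 x 10 / 60 = 875 hours and the fully replaced case is 750 x 7 x (-5) / 60 = about -438 hours. Even 1,250 hours is 1,250 / (15 x 10) = 8.3 hours per RHC per month, or about 1 hour per worker among 8. This stands: ten virtual contacts for every patient is an upper end, and the figures do not show that staff time is a dominant cost.

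It could also be said that time valuation is detail for an analysis plan. That would answer silence. Here the Protocol states a rule, and the rule conflicts with its own perspective.

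A reader might infer two further things that the documents do not support. One is that peer-group calls use unpaid RHC time; section 4.3.4 describes them as patient groups supported by patient champions and does not say that staff run them. The other is that the budget impact analysis inherits the error; the Phase III section bases it on project and annual implementation costs, does not import the salary rule, and asks about affordability, for which salaries already being paid need not be new expenditure.

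**Conclusion.** The conflict is real and lies within section 4.5: the salary rule, read naturally, leaves out in-hours RHC staff time that a societal perspective must count, and gives no credit for time released. The incremental cost and the ratio would therefore not be what their label says.

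A reader might go further and conclude that the ratio is biased in the package's favour. The documents do not support that. The consultation component has no fixed sign, because it depends on how many visits are replaced and how long they last. The size of the mentoring component depends on hours that are not given and on what is already booked as training. The hours shown rest on assumed contact lengths and frequencies, and they cannot be turned into money without wages. What can be said is that direction and size are undetermined. The effect is confined to the economic part of objective 3; the primary systolic blood pressure comparison is untouched.

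**What to change.** Replace the salary sentence in section 4.5 with wording to this effect: RHC staff time for face-to-face and virtual consultations, and for mentoring not already counted under training costs, will be valued at salary cost in both arms, whether or not extra hours were sought.

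The inputs are largely in place. Contact counts come from the treatment cards, which record physical and virtual consultations (sections 4.3.5 and 4.6). Mentoring hours come from project records, since the cards do not hold them. Minutes per contact type come from the manager interviews already planned, which should also ask about COVID triage and case management done outside a recorded contact. Peer-group calls should be left out unless staff are shown to run them. Report extra-hours-only costing as a sensitivity analysis.

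The alternative is to keep the rule and declare a perspective narrower than societal, stating that in-hours staff time is excluded.

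The cost is a wording change, some added interview questions, salary rates, and a check against double-counting training. The downsides are that minutes per contact will be managers' estimates, and that the incremental cost may look less favourable.

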#### **4.6 Data collection, management, and analysis**

We will collect patients' demographic and social information, their exact home address, blood pressures, body weight, and height, knowledge, attitude and practice (KAP) regarding NCD and COVID at the randomization and Month 10 in the RHCs. The RHC doctor will measure the participants' blood pressure using a calibrated electronic blood pressure apparatus after 5 minutes of seated rest, and measure body weight and height. Participants will be asked to provide a blood sample in the RHC at the recruitment and Month 10. In addition, we will also collect patient blood pressures in Month 10 using same methods. Blood samples will be collected and analyzed in RHC according to national guidelines for fasting blood glucose. We will collect attendance rates using the routine patient treatment cards in RHCs to record both physical and virtual consultations. We will conduct a survey at the recruitment to collect patient demographics, socioeconomics, smoking status, COVID-19 immunization status, health service use, medial, KAPs for NCD and COVID, and health care and related costs. The survey will be repeated at Month 10 in the last follow-up to collection information regarding COVID-19 symptoms and related health care consultation and use. Any deaths that occur in patient group during this period will be assigned a probable cause, as determined by a method called verbal autopsy.

Overall, we will conduct mixed methods evaluation to examine the utility of the NCD-COVID guideline, the platforms and care process to inform acceptability, feasibility, reach, adoption, and implementation related challenges (in Section 5.2).

We will present appropriate descriptive statistics for RHCs and individual level, along with appropriate summary statistics and their associated 95% confidence intervals for all the outcomes. Then, for all outcomes, we will produce a main set of estimates of intervention effectiveness using cluster-level methods of analysis suitable for cluster trials. In particular, a linear mixed effect model will be used to analyse the primary outcome (systolic blood pressure) adjusting for the baseline systolic blood pressure. For other continuous secondary outcomes a similar analysis will be employed. Binary secondary outcomes will be analysed with the generalized estimating equation (GEE) approach, employing a binomial family with logit link function and exchangeable working correlation structure on sites. There will no interim analyses. Intent to treat analysis will be conducted.

**4.4 Phase III: Evaluation and Knowledge Dissemination (Objective 3&4) (3 months):** The phase III will also be used to complete the outcome evaluation, process and cost-effective evaluations highlighted in phase II. We will work together to 1) compile and analyze quantitative and qualitative data in Pakistan and Canada and produce reports and papers; and 2) coordinate with Department of Health Services at the provincial and national levels to translate evidence into program decisions for providing integrated COVID-NCD care in Pakistan and other LMICs. In addition, we will conduct four activities regarding the success factors for scaling up our interventions in LMICs: 1) budget impact analysis: we will review the project costs, and estimate the annual costs for implementation which will inform the affordability in the health system; 2) develop a practical monitoring framework with multi-stakeholders, to inform its usability for future scale-up to other countries; 3) document factors that either facilitate or hinder scale-ups; and 4) provide detailed scale-up plans. The results of the implementation and scale-up will be communicated to policy makers by constantly engaging them in all the stages of the study using workshops, meetings and policy briefs. We will publish the results in leading academic journals and provide policy briefs to policymakers.

**5. Project management:** The investigators will seek ethical approvals from the Research Governance Committees in Canada and Pakistan (if needed). The study will be conducted to protect human rights and dignity of the participants. The study has been designed to minimize the burden of participants and any foreseeable risks in relation with the interventions. Interventions of our care program have no known harms. Starting from the usual care period, all participant patients will receive study information in Urdu and English and be invited to participate in the study by research staff in RHCs. We will collect written consents where feasible. We will collect informed consents from all participants. [name] and [name] will be co-guarantees who have full access to the trial dataset. A trial management unit (TMU) will be established in Islamabad, Pakistan with a trial manager and one staff locally and a research coordinator from UofT. TMU will manage the day-to-day activities of the trial. [name] will be the lead statistician, supported by [name]. External member led DSMC will be established to safeguard the safety and privacy of patients involved, and to ensure that all data are collected according to agreed ethical guidelines, properly stored and only used for research purposes. A trial steering committee (TSC) will be established and led by external members. We will organise teleconference meetings for both the DSMC and TSC at the beginning of the study, and then on quarterly basis. The committees may also meet on an ad hoc basis should the need arise.

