transmission of COVID. In the context, care for patients living with diabetes/ hypertension must address their COVID needs, while continuing NCD care with minimal transmission risk. This needs increased skills of health providers in identification and diagnosis of NCD cases and improved triage, diagnosis, treatment and referral services for NCD in intervention population. A remote training and monitoring platform is equally important to maintain high quality of care in LMICs. Our previous studies demonstrated the feasibility and effectiveness of a community-based hypertension/ diabetes management in Pakistan. The Extension for Community Healthcare Outcomes (ECHO), a remote training and mentoring system, was proved effective to improve NCD management. We have successfully conducted online training of COVID-19 in primary healthcare facilities in Asia and Africa. There is a high need in LMICs for evidence regarding the feasibility and effectiveness of an integrated COVID-NCD prevention and care that is guided by implementation science frameworks.

**2. Hypothesis, Aims and Objectives:** We aim to design a package of integrated Covid-NCD care in RHCs of Punjab Province, Pakistan. Based on our existing NCD projects in Punjab, we will adapt our COVID-19 primary care guidelines developed in other LMICs, to integrate COVID-19 vaccination, health education, case management and support for patients with hypertension/ diabetes. Our study is guided by the implementation science RE-AIM framework, which tackles health system factors at multiple levels. Our overall aim is to reduce patient overload at hospitals, avoid nosocomial transmission, reduce community transmission, and provide patient support.

**Specific objectives** include: 1) to conduct a rapid context analysis at primary care level by focusing on issues relating to how to embed COVID-19 care into the existing NCD programs in RHCs; 2) to evaluate the effectiveness of the integrated COVID-NCD care package based on clustered randomized controlled trial; 3) to conduct process evaluation and cost-effectiveness analysis that is embedded in the project to facilitate future scaling up the evidence in Pakistan and other LMICs; 4) to plan, prepare for scale-up the package in Pakistan and other LMICs.

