**4.3.6 Sample size and justification:** Sample size is based on demonstrating the intervention achieves a non-inferior result in systolic blood pressure (SBP). We will define a non-inferiority margin of 2.5 mmHg. The reasoning behind this is that SBP can be quite variable over the day, easily ranging 5 mmHg. Thus, if the intervention results in SBP no worse than control by 2.5 mmHg, it would represent non-inferiority. Based on prior work, the standard deviation of SBP is expected to be about 11 mmHg. For an individually randomized trial, a sample size of 332 per group would have 90% power with a one-sided type one error of 5% to demonstrate non-inferiority at a 2.5 mmHg margin. We will aim to recruit 40 patients per cluster. If we assume a modest intra-class correlation (ICC) of 0.03, indicating a sample size of 614 per group to achieve the same power. Thus, 15 clusters per group of 40 patients each will be required to obtain the minimal required sample size. Considering a 20% loss-to-follow-up rate based on our trials in Pakistani and China, we aim to increase to 50 patients per cluster, that is a total of 1500 patients to be recruited. Power will increase if all clusters meet the enrollment target of 50 patients; furthermore, the impact of averaging each patient's systolic blood pressure over the last 3 months should reduce the standard deviation, further increasing power. The reason for averaging is that single systolic blood pressure measurements are less representative of blood pressure.

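### The protocol sizes the trial for non-inferiority in systolic blood pressure, but its objective and analysis text speak only of effectiveness and never use the 2.5 mmHg margin

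*Protocol*

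**What the plan says.** Section 4.3.6 bases the sample size on showing that systolic blood pressure (SBP) is not worse under the intervention. It sets the margin, "We will define a non-inferiority margin of 2.5 mmHg", and the error rates: 332 per group gives "90% power with a one-sided type one error of 5% to demonstrate non-inferiority at a 2.5 mmHg margin". It then moves to 614 per group for an ICC of 0.03 and to 15 clusters of 40 per arm.

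The other parts that bear on the primary endpoint use different language:

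- **Section 2, objective 2:** "to evaluate the effectiveness of the integrated COVID-NCD care package based on clustered randomized controlled trial".
- **Section 4.3.5** presents SBP as an indicator of effectiveness.
- **Section 4.6** gives descriptive statistics "along with appropriate summary statistics and their associated 95% confidence intervals for all the outcomes". It then promises main estimates of effectiveness, with a linear mixed model for SBP adjusted for baseline, and adds "Intent to treat analysis will be conducted".

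In the protocol text available (the part between sections 2 and 4 is not), non-inferiority, the margin and the one-sided 5% level appear only in section 4.3.6.

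**The concern.** A trial needs one primary hypothesis, and it should be the one that was powered. Here the sizing section sets out to show that SBP is no worse by 2.5 mmHg or more, while the objective and analysis text read as a search for an effect. These are different questions with different decision rules. A non-significant difference in an effectiveness analysis does not show non-inferiority, and section 4.6 gives no rule that would.

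The interval level is also unsettled. A one-sided 5% test corresponds to a two-sided 90% interval, yet 95% is the only level named. The verdict on the primary endpoint could therefore depend on which section is followed. If the question stays open, it could be settled after results are seen, in a trial whose health centres are not blinded.

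**Working it through.** **Inputs (section 4.3.6).** Margin 2.5 mmHg; SD 11 mmHg ("the standard deviation of SBP is expected to be about 11 mmHg"); one-sided alpha 5%; power 90%; ICC 0.03; 15 clusters of 40 per arm; 614 per group after clustering.

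**1. Reproduce the plan's figure.** With a true difference of zero,

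n = 2 × (1.645 + 1.282)² × 11² / 2.5² = 332 per group.

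This matches the protocol. It also shows that the planning case is no true difference. Under that case a two-sided 5% superiority test would find benefit only 2.5% of the time, so the effectiveness reading is not what the trial was sized for.

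**2. The same step at one-sided 2.5%** (a two-sided 95% interval read against the margin):

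n = 2 × (1.960 + 1.282)² × 11² / 2.5² = 407 per group.

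**3. Effect of the interval level on the protocol's own 614.** The implied design effect is 614/332 = 1.85, so the effective size is 332 per group.

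SE = 11 × √(2/332) = 0.854, and 2.5/0.854 = 2.928.

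- One-sided 5%: Φ(2.928 − 1.645) = 90.0%.
- One-sided 2.5%: Φ(2.928 − 1.960) = 83.4%.

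**4. The same with the stated ICC and 15 × 40 per arm.** Design effect = 1 + 39 × 0.03 = 2.17; effective size = 600/2.17 = 276.5.

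SE = 11 × √(2/276.5) = 0.936, and 2.5/0.936 = 2.672.

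| Decision interval | Normal | t, 28 df |
|---|---|---|
| Two-sided 90% (one-sided 5%) | 84.8% | 83.2% |
| Two-sided 95% (one-sided 2.5%) | 76.2% | 73.2% |

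The gap between 90% and 85% in the first row has nothing to do with the interval. It arises because 614 does not follow from the stated ICC: 332 × 2.17 = 720. Only the step from 85% to 76% belongs to this point.

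**5. How the verdict can turn** (hypothetical estimates, SE 0.936, normal limits).

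- Estimate +0.8 mmHg: the upper 90% limit is 0.8 + 1.645 × 0.936 = 2.34, below the margin. The upper 95% limit is 0.8 + 1.960 × 0.936 = 2.63, above it.
- Estimate +1.0 mmHg: the 95% interval is −0.8 to 2.8, so there is no significant difference. The upper 90% limit is 2.54, so non-inferiority is not shown either.

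**The case against.** The best defence has several parts.

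**The hypothesis is already fixed.** Section 4.3.6 sets the margin, alpha and sidedness in advance, effectiveness is a loose word, and the mixed model yields the estimate needed either way. A statistical analysis plan, not at hand, may state the decision rule. This limits the repair to wording, but it does not remove the contradiction. The type of primary hypothesis belongs in the protocol, and an analysis plan that followed the objective and section 4.6 would not test non-inferiority.

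**The 95% intervals are descriptive.** A reader might infer that non-inferiority will be judged at the wrong error rate. The text does not say so: the intervals accompany summary statistics, and the sentence on effect estimates gives no level. If they were used, the test would be stricter, so the cost would be power and not false claims. This stands.

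**The power loss can be overstated.** A reader might set 76% against the stated 90% and blame the interval. Part of that gap is the separate clustering error. The SE above also ignores baseline adjustment and three-month averaging. As an assumption, a baseline correlation of 0.4 to 0.5 that cuts the variance by 16% to 25% would bring power at one-sided 2.5% to about 83% to 87%. This stands too.

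**Uptake and intention to treat.** Section 4.3.8 lists "non-compliance of health providers and patients" as a source of bias, and virtual consultation is optional. A reader might infer that intention to treat is the only analysis and that low uptake could manufacture non-inferiority. The documents do not support that. Section 4.6 does not exclude other analysis sets, and supportive sets may sit in the analysis plan. The package also acts at facility level through guidelines and staff training, so patients who decline virtual visits do not simply receive control care. Dilution scenarios need harms and uptake rates that the protocol does not give. For the effect of offering the package, a diluted average difference inside the margin is a correct non-inferiority finding.

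**Conclusion.** The point holds as a contradiction about the primary hypothesis. The trial is sized only for non-inferiority at 2.5 mmHg, while objective 2 and section 4.6 frame the endpoint as effectiveness, name 95% as the only interval level and never use the margin. It should be resolved before analysis, because it determines what the trial can conclude.

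The numerical consequence is conditional. If a 95% interval were used for the decision, power would be about 83% instead of 90% on the protocol's own 614 per group. At 15 × 40 per arm with ICC 0.03, it would be about 76% (t: 73%) instead of about 85% (t: 83%). These figures assume SD 11 mmHg, a true difference of zero, equal cluster sizes and no gain from baseline adjustment or averaging. No inflation of type I error is shown, and the absence of a per-protocol analysis is not part of the finding.

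**What to change.** In sections 2 and 4.6, state that the primary hypothesis is non-inferiority of the intervention in SBP. Conclude it if the upper limit of the two-sided 90% confidence interval for intervention minus control, from the baseline-adjusted mixed model, is below 2.5 mmHg. Test superiority only after non-inferiority is shown.

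If the team prefers a 95% interval for this decision, keep the same rule but restate the power as above, or redo the sample size from 407 per group before clustering (407 × 2.17 = 883 per group at ICC 0.03 and 40 per cluster). In either case the step from 332 to 614 needs its own correction, since a 90% interval alone does not restore 90% power at the stated ICC.

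The first option costs a few sentences and no new data. The 95% option costs stated power or more clusters. An adherence-based analysis from the attendance records already planned could be added as supportive, but it should not be a condition for the claim because it is not a randomised comparison.
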